## Abstract

Reduced appetite with ageing is a key factor that may increase risk of undernutrition. The objective of this study is to determine the impact of innovative plant protein fibre (PPF) products within a personalised optimised diet (PD), a physical activity (PA) programme, and their combination on appetite, and other nutritional, functional and clinical outcomes in community-dwelling older adults in a multi-country randomised controlled intervention trial. One hundred and eighty community-dwelling adults (approximately sixty per trial centre in Germany, Ireland and Italy) aged 65 years and over will be recruited to participate in a 12-week, parallel-group, controlled trial. Participants will be randomised into one of four groups: 1, PD (incorporating two PPF products): 2, PA; 3, PD + PA; and 4, no intervention (control). The primary outcome is appetite measured by visual analogue scales and energy intake from an *ad libitum* test meal. Secondary outcomes include fasting and postprandial appetite-related gut hormones, Simplified Nutritional Appetite Questionnaire score, body composition, cardiorespiratory fitness, muscle strength, physical function and PA. In addition, self-efficacy, cognitive status, dietary restraint, depressive symptoms and compliance and acceptability of the intervention will be assessed. Metabolomic profiles, RMR, muscle motor unit properties and gut microbiome will also be assessed to explore potential underlying mechanisms. This multi-centre randomised controlled trial will advance knowledge on how PD (incorporating PPF products), PA and their combination influence appetite, nutritional status and related health outcomes in community-dwelling older adults and contribute to the prevention of undernutrition. **Trial registration:** Clinical Trials.gov Registry NCT05608707 (registered on 2 November 2022). **Protocol Version:** NCT05608707 Version 4 (registered on 29 September 2023).

Older adults are at high risk of poor appetite and undernutrition, which can lead to frailty, sarcopenia and poor health outcomes^(1–7)^. Although definitions of appetite vary^(8)^, reduced appetite and food intake occurs even in healthy older adults and manifests alongside reductions in muscle mass^(3,6,9,10)^. A meta-analysis of fifty-nine studies comparing healthy older with younger adults reported hunger to be 25 % (fasting) to 39 % (postprandial) lower and energy intake to be 16–20 % lower in the older adults^(10)^.

Multiple environmental, psychological and physiological factors are implicated in appetite deterioration in older adults. For example, social isolation, depression, loss of pleasure in food and taste decline all contribute to reduced appetite^(11–13)^. Physiological factors include altered gut and other peripheral hormones related to appetite, reduced gut motility, inflammation and changes in the central control of food intake^(11,14)^. Reduced fat-free mass and resting energy expenditure and an altered gut microbiome have also been implicated as determinants of reduced appetite in older adults^(12,15,16)^, although evidence of causal associations is currently limited. Multicomponent intervention strategies are therefore needed to address appetite decline and prevent undernutrition^(2,12)^.

The need for interventions to address reduced appetite in older adults, or to increase dietary intake despite a reduced appetite, has been clearly recognised and should be a key target for reducing nutrient deficiencies and risk of undernutrition^(15,17)^. However, current pharmacological interventions have limited utility in clinical practice^(15)^. Appropriate nutrition and exercise are considered the optimal strategies to limit declines in muscle mass and function with ageing^(18,19)^. Adequate protein and dietary fibre intakes are essential for healthy ageing. Adequate protein intake is important to reduce age-related declines in muscle mass, strength and function^(20,21)^. Adequate fibre intake is associated with normal bowel function, reduced intestinal transit times and reduced risk of several non-communicable diseases, among other health benefits^(22–24)^. For older adults, daily consumption of at least 1·0–1·2 g/kg body weight of protein^(18,19)^ and 25–30 g of fibre^(24,25)^ is recommended. However, intakes of both nutrients are often sub-optimal in European older adults^(23,26–31)^, including in those with poor appetite^(27)^. In a cross-sectional analysis of over 2500 community-dwelling older adults, those with a poor appetite were found to have a lower intake of protein and dietary fibre compared with those with good appetite, after adjustment for energy intake and other potential confounders^(27)^.

With regard to effects on appetite and energy intake, a systematic review of acute and longitudinal studies found protein supplementation (through supplements or whole foods) has no negative impact on overall energy intake in older adults^(32)^. Similarly, a systematic review of thirty-eight different fibre sources found most isolated fibres did not acutely suppress appetite or energy intake in the general population and a recent 10-week intervention in older adults demonstrated pea hull fibre (10 g/d) supplementation did not suppress appetite^(33,34)^. Interestingly, older adults with poor appetite also appear to have a preference towards non-dairy and high-fibre foods^(35)^. Therefore, addition of plant protein and fibre to the habitual diet appears a promising strategy to improve intake of these nutrients and enhance related health outcomes. Both nutrients may impact several mechanisms implicated in appetite decline with ageing such as alterations in gut motility, inflammation, fat-free mass and the gut microbiome and metabolite profiles^(11,14,16,24,36–41)^. However, further longitudinal studies examining the effect of protein and fibre on appetite and energy intake in older adults are needed.

There is debate surrounding optimal protein sources to support healthy ageing. Although plant proteins are generally characterised by a lower content of essential amino acids, a meta-analysis of nine studies (including three studies in adults aged over 50 years) found longer-term supplementation with animal or plant protein combined with resistance exercise produced similar effects on lean mass and strength^(42)^. Furthermore, evidence from cell and animal models suggests that insoluble fibre may enhance *de novo* amino acid biosynthesis via alterations in the gut microbiome^(41,43)^, which would support combining plant protein with fibre supplementation. Plant proteins are also well accepted by older adults and more environmentally sustainable^(44,45)^.

Consensus guidelines on nutrition for older adults highlight the importance of individualised nutrition interventions and recommend including additional non-dietary factors such as physical activity (PA) or social aspects^(2)^. In healthy older adults, most benefits of protein supplementation are only observed when combined with exercise^(46)^. There is initial evidence that whey protein supplementation combined with exercise can increase energy intake in older adults^(36)^. Elsewhere, it has been hypothesised that increasing PA may benefit appetite and energy intake, although the evidence base to support this is currently limited^(47,48)^.

The innovative plAnt Protein fibre and Physical activity solutions to address poor appEtite and prevenT undernutrITion in oldEr adults (APPETITE) randomised controlled trial (RCT) aims to determine the impact of a personalised optimised diet (including innovative plant protein fibre (PPF) products), a PA programme, and their combination on appetite and other nutritional, functional, metabolic and clinical outcomes in community-dwelling older adults. The multi-country trial is part of the European APPETITE project, funded under the Horizon Joint Programming Initiative ‘A Healthy Diet for a Healthy Life’^(49)^.

## Methods and analysis

The protocol is written in accordance with the Standard Protocol Items: Recommendations for Interventional Trials (SPIRIT) guidelines^(50)^. A summary checklist is reported in Appendix 1(online Supplemental Appendix 1). The composition, roles and responsibilities of the coordinating centre, individuals overseeing the trial and external advisory board are listed in Appendix 2 (online Supplemental Appendix 2).

### Study design

The trial is a multi-centre RCT aiming to recruit 180 community-dwelling older adults (about 60 per centre) in Nuremberg – Germany, Dublin – Ireland and Padua – Italy, all urban settings. Employing a 2 × 2 factorial parallel-group design, outcome measures will be assessed pre and post a 12-week intervention. Participants will be randomly allocated (1:1:1:1) by study centre and sex to one of four groups: Personalised diet (PD): daily consumption of two PPF products and dietary counselling over a 12-week period;PA: group exercise classes twice per week and home-based walking over a 12-week period;PD and PA: both interventions described above combined;Control: no intervention, usual diet and PA.

An overview of the timeline for participants is shown in Fig. 1.

**Fig. 1. f1:**
[figure not shown]
Overview of timing of screening, intervention and assessments. Primary outcomes are assessed at baseline and week 13. Created in Biorender.com

Screening (telephone followed by in-person) and baseline (pre-intervention) assessments will be completed within 6 weeks prior to commencing the trial. The intervention duration lasts 12 weeks. Post-intervention testing will be performed in the week following the intervention. In groups involving PD, participants will be required to consume PPF supplements and in groups involving PA to complete home-based walking up to and including the day prior to returning for the final outcome assessment, respectively.

#### Sample size

Sample size calculations were conducted in G * Power (version 3.1). A 120 kcal (500 kJ) difference in *ad libitum* test meal energy intake and a 10 mm change in visual analogue scale (VAS) appetite ratings have previously been considered physiologically relevant differences^(8,51)^. To allow for 20–25 % dropout, a sample size of 180 participants (45 per group) is sufficient to detect these differences between groups, allowing for 10 % variance on a within participant sd of change in *ad libitum* test meal energy intake of 143 kcal ^(36,52)^, and for VAS of about 13 mm, observed in our unpublished data, similar to others^(36)^, at 80 % power and significance at *P* < 0·05.

#### Recruitment and eligibility of study participants

Multiple recruitment strategies will be employed including flyers, social media and newspaper advertisements. If recruitment does not meet targets in one centre, this may be compensated for by additional recruitment at another centre. Interested individuals will be provided with a participant information sheet, and if still interested and potentially eligible will complete telephone screening with a trained researcher. Persons who are still eligible after telephone screening will subsequently be invited to complete an in-person screening at the study centre. Criteria to determine participant eligibility are shown in Table 1. Medical conditions and medications for exclusion are listed in Appendix 3 (online Supplemental Appendix 3). Due to initially very slow recruitment, age was lowered from originally >/= 70 years, a Simplified Nutritional Appetite Questionnaire (SNAQ) score </=14 removed (both April 2023) and BMI widened from 22 to 27 kg/m^2^ (August 2023). Most previous studies examining appetite in older groups and showing reduced appetite and energy intake compared with younger groups involved older adults aged 60–65 years and older^(10)^.

**Table 1. tbl1:** APPETITE trial inclusion and exclusion criteria

Inclusion criteria	Exclusion criteria
• >/=65 years of age • Community-dwelling • BMI 20–30 kg/m^2^ • Inactive (<150 min moderate or vigorous activity/week) • Have proof of COVID-19 vaccination	• MMSE </= 24 • CES-D > 16 • Weight loss (intentional or unintentional) >5 % within last 3 months (participant self-report) • Heavy smoker (>10 cigarettes per d or vape equivalent) • Medical condition or medication known to impact on appetite or energy intake • Other medical condition that may impact on ability to participate in study or study outcomes • Planned relocation within the next 6 months • Inability to travel to study centre/PA location • Currently participating in another intervention study • Currently participating in regular resistance training > once per week • Inability to participate in physical activity • Unable to walk across a room • Allergic and/or unwilling to consume study test food • Loss of taste or smell associated with COVID-19 • Unwilling to accept randomisation to any study group

MMSE, Mini Mental State Examination; CES-D, Centre of Epidemiology Study – Depression (CES-D) questionnaire; PA, physical activity.

### Randomisation, blinding and study allocation

Participants will be randomised upon meeting all eligibility criteria on completion of in-person screening and will be informed of their allocated group after baseline data have been collected. Randomisation will be stratified by study centre and sex. If a participant is identified as ineligible after randomisation and prior to baseline assessment due to error in screening^(53)^, a participant of the same sex will be randomised to the group the ineligible participant was allocated to. If members of the same household are eligible, they will be stratified to the same group. Randomisation will be centralised and conducted by an independent researcher, not connected to the project, using the QMINIM platform (Telethon Kids Institute, Australia). For the duration of the intervention and post-intervention assessments, both participants and researchers are unblinded to intervention allocation.

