The time required to improve some of the outcomes assessed is unclear and may require a longer duration than the 12-week intervention in the APPETITE RCT; however, effects of protein supplementation and exercise on appetite have previously been demonstrated in 12-week trials across various populations^(36,91)^.

Due to the nature of the intervention, one limitation is that it is not possible to blind participants to treatment allocation. An additional limitation is the lack of blinding of researchers who are involved in both the administration of the intervention and data collection due to logistical constraints. However, data will be analysed anonymously by a blinded researcher to minimise detection bias.

In summary, the APPETITE multi-centre RCT will provide novel insight on the impact of PD (incorporating PPF products), PA and their combination on appetite, and other nutritional, functional, clinical and metabolic outcomes in community-dwelling older adults. This will advance knowledge on how these interventions influence appetite, dietary intake and nutritional status and contribute to future research in the field. This will ultimately inform guidelines to contribute to a better nutritional status and quality of life for older Europeans.

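### A participant who replaces one found ineligible is placed in the vacated group, not randomised; the rule names sex but not centre, and concealment from enrolling staff is not stated for this step

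*Protocol article*

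**What the plan says.** Under Study design, the protocol article sets the allocation: "Participants will be randomly allocated (1:1:1:1) by study centre and sex to one of four groups". Under Randomisation, blinding and study allocation it repeats the factors: "Randomisation will be stratified by study centre and sex".

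The latter section then makes an exception. The trigger is narrow: "If a participant is identified as ineligible after randomisation and prior to baseline assessment due to error in screening". When it fires, "a participant of the same sex will be randomised to the group the ineligible participant was allocated to". The next sentence adds a second form of direct placement: eligible members of one household go to the same group.

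Three statements bear on who knows what, and when:

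- Allocation is handled away from the sites: "Randomisation will be centralised and conducted by an independent researcher, not connected to the project, using the QMINIM platform".
- Participants "will be informed of their allocated group after baseline data have been collected".
- On blinding: "For the duration of the intervention and post-intervention assessments, both participants and researchers are unblinded to intervention allocation".

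The Discussion gives as a limitation the "lack of blinding of researchers who are involved in both the administration of the intervention and data collection". Trial status reports that recruitment ended in April 2024 and that the last final visit was in July 2024.

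**The concern.** Nobody can be randomised to a group that is already named. The replacement inherits another person's allocation, so the article's description of the step is wrong as it stands.

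The practical worry is selection. Under ordinary allocation, staff who know every earlier assignment still cannot be sure of the next one. Under this rule, anyone who knows the vacated group knows where the next replacement of that sex will go. The rule also does not say that the replacement must be the next eligible person in sequence, which leaves room for choice. If staff have that knowledge and that choice, the type of person enrolled can depend on the group.

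This matters more here than in a blinded trial. Participants and researchers know the groups during the intervention, and one of the two joint primary outcomes is a self-rated appetite score. The analyst is to be blinded (Discussion), but that does not protect who enters which group.

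The omission of centre is a separate flaw. Allocation is balanced on centre and sex, and the replacement rule as written preserves only sex.

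**Working it through.** **1. Is the replacement randomised?** Under 1:1:1:1 allocation a new participant has probability 1/4 = 0.25 of each group. Under the rule, given the vacated group, the probability of that group is 1 and of the others 0. No new draw takes place.

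**2. Is centre preserved?** The allocation factors are centre and sex (Study design; Randomisation, blinding and study allocation). The replacement is matched on sex. Centre is neither required nor excluded.

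**3. Is the vacated group concealed from enrolling staff?** In order of time:

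- Randomisation follows in-person screening and is done centrally.
- The trigger falls after that and before baseline assessment.
- Participants learn their group after baseline data collection.
- Unblinding of researchers is stated for the intervention and post-intervention period.

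For the interval in which the rule operates, the article says when participants are told. It does not say what screening or enrolling staff know.

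**4. The plan's own sample size.** Inputs from Sample size: 120 kcal and SD of change 143 kcal; 10 mm and SD 13 mm; 80% power; 0.05 (taken as two-sided); dropout 20–25%; 45 per group, 180 in total. The 10% allowance is read as applying to the SD, giving 143 × 1.1 = 157.3 kcal and 13 × 1.1 = 14.3 mm. A two-sample t-test then needs:

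| Outcome | n per group | n/(1 − 0.25) |
|---|---|---|
| Energy intake | 28 | 38 |
| VAS | 34 | 46 |

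The stated 45 is reproduced to within one per group (4 × 46 = 184 against 180). The replacement rule does not alter it.

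**5. Possible size of a shift.** The number of replacements k is not in the document. Assume k = 2 to 5, all in one arm, each differing by 0.5 SD in expected change in the same direction, and lost to follow-up at the same rate as others.

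Shift in SD = (k / n) × 0.5; shift in kcal = that × 157.3.

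| k | Arm of 45 | Margin of 90 (two arms) |
|---|---|---|
| 2 | 2/45 × 0.5 = 0.022 SD = 3.5 kcal | 2/90 × 0.5 = 0.011 SD = 1.7 kcal |
| 5 | 5/45 × 0.5 = 0.056 SD = 8.7 kcal | 5/90 × 0.5 = 0.028 SD = 4.4 kcal |

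Against the 120 kcal target, the arm figures are 3.5/120 = 3% and 8.7/120 = 7%. On the VAS the same fractions give 0.022 × 14.3 = 0.3 mm and 0.056 × 14.3 = 0.8 mm, against a target of 10 mm.

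As a wider assumption, 9 replacements would be 9/180 = 5% of the trial. If all fell in one margin, the shift would be 9/90 × 0.5 = 0.05 SD. If there were no replacements, the shift is zero.

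**The case against.** The strongest reply is that the vacated group was itself drawn by the central randomisation. If it stays hidden from enrolling staff and the next eligible person of that sex takes it, that person's group is still a matter of chance and unrelated to their characteristics. No selection bias follows, and the contrast of 1 with 0.25 exists only for someone who knows the vacated group. This is correct, and it means that any bias depends on knowledge the article does not report.

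A reader might infer that the next assignment is foreseeable outright. The document does not support that. Allocation is central and independent, the rule fires before baseline, participants have not yet been told, and unblinding is stated only for later stages. The Discussion's remark on unblinded researchers concerns delivery and data collection, not enrolment. What remains is that concealment from enrolling staff is not stated for this step.

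A reader might also infer that replacements cross centres. The article does not say so. A same-centre replacement is a natural reading, and the provision for recruiting more at another centre concerns missed targets. What remains is that the rule as worded omits one of its two stratification factors.

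A third inference would be that the rule is redundant because the platform corrects imbalance automatically. The article names the platform but does not describe its algorithm, so this cannot be relied on.

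Finally, the article condenses a fuller protocol, and the trigger clause cites a source that is not at hand. Operational detail may exist elsewhere. But the rule is stated here and described as randomisation, so correcting it does not depend on unseen text.

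**Conclusion.** The point holds in a limited form. A replacement is placed in a predetermined group, the rule mentions sex but not centre, and the article does not state that enrolling staff are unaware of the vacated group. Foreseeability is a conditional risk, not an established fault.

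The likely effect is small: about 3.5 to 9 kcal in an arm of 45 and about half that in a factorial margin of 90. Those figures rest on assumed inputs: 2 to 5 replacements, all in one arm, all shifted 0.5 SD the same way, with an SD of 157.3 kcal. The true number may be zero. The case for acting rests on the integrity of allocation and on transparent reporting, not on a large expected bias.

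The household rule raises the same question where a second member enrols later: that person's group is fixed by the first member's, which the first member learns after baseline. The article does not say whether household members enrol together, so this too needs only counting and a sensitivity analysis.

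**What to change.** In the protocol, replace the rule with normal allocation: the next eligible participant is allocated by the central procedure within centre and sex, and the person found ineligible is recorded as a post-randomisation exclusion in the group drawn.

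Recruitment has closed, so for this trial the useful steps are in analysis and reporting:

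1. Flag every directly placed participant: replacements, and household members enrolled after the first.
2. Report their number by group and centre. If no replacements occurred, one sentence settles that part.
3. State whether enrolling staff knew the vacated group when a replacement was chosen, and whether replacements came from the same centre.
4. Repeat the primary analysis of both joint primary outcomes without the flagged participants, as a sensitivity analysis.

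The cost is one extra analysis and a few lines of reporting. Had normal allocation been used from the start, the price would have been slightly less exact group sizes.

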### Data management and statistical analysis plan

All data will be collected on questionnaires and record sheets in a de-identified manner using a participant ID number and stored securely according to General Data Protection Regulation (2018)^(84)^ at each site, with electronic data double-entry into a central electronic database stored and backed up at one site (Ireland). The trial coordinating centre Principal Investigators will have access to the full dataset across all sites. Study site Principal Investigators will have direct access to the dataset at their own site and will have access to data from other sites by request. Anonymised data will be made available to other researchers on reasonable request after the main trial manuscript is published.

There are no plans for interim study analysis. After completion of the study data collection, data will be checked and cleaned using descriptive statistics and data visualisation. Outcome data will first be analysed according to the intention-to-treat principle, using a random coefficients generalised linear mixed model for primary and secondary end points. The effects of time, the two interventions and their interaction (following the 2 × 2 factorial design of the trial) and sex will be included as fixed effects. Participant ID and study site will be included as random effects. Residuals will be tested for normality and transformation applied where required, or where the structure of the data is inherently non-normal. 95 % CI will be reported where applicable. Per-protocol analyses and mediation analyses will be conducted to examine to what extent compliance and potential mediating mechanisms explain the impact on the primary and secondary end points. For primary pre-planned contrasts, significance will be accepted as *P* < 0·05. Where groups of secondary outcomes are analysed, the significance level will be adjusted by Bonferroni correction according to the number of responses in the analysis. A correlation matrix will be constructed to assess relationships between outcome variables. Missing data will not be imputed in the primary analysis. Intention-to-treat analyses will be based on the *as-observed* population.

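### Eligible household members share one group, but the stated model has no household term, so any co-enrolled members would be analysed as independently allocated

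*Protocol article*

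**What the plan says.** Under Randomisation, blinding and study allocation, the protocol article states: "Randomisation will be stratified by study centre and sex". It then adds the household rule: "If members of the same household are eligible, they will be stratified to the same group". Household is not one of the stratification factors, so the rule can only mean that eligible members of one household receive the same allocation.

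Under Data management and statistical analysis plan, outcomes are to be analysed "using a random coefficients generalised linear mixed model for primary and secondary end points". The terms are listed. The fixed part of the model holds time, each intervention, the product of the two, and sex. For the random part the article says: "Participant ID and study site will be included as random effects". No household term and no cluster-robust variance is named.

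The Sample size section has no allowance for shared households.

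**The concern.** A participant effect handles the two measurements on one person, and a site effect handles centre. Neither absorbs correlation between two people who live together. Members of one household plausibly eat together, and in the activity groups may walk or attend classes together, so their changes over 12 weeks may be alike.

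When such pairs always sit in the same group, positive correlation inflates the variance of every group mean and does not cancel from the contrasts, as it could if partners were split between groups. A model that ignores this gives confidence intervals that are too narrow and a type I error above the stated 5%. The same model serves both joint primary outcomes and the secondary outcomes.

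**Working it through.** **1. The plan's own sample size.** Inputs from the Sample size section: a 10 mm VAS difference, SD of change about 13 mm, a 10% allowance (applied here to the SD: 13 × 1.1 = 14.3), 80% power and 20–25% dropout. Two-sided 5% is assumed, since sidedness is not stated.

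- Normal formula: n = 2 × (1.96 + 0.84)² × 14.3² / 10², rounded up to 33 per group. The t-test version gives 34.
- With 25% dropout: 33/0.75 = 44 and 34/0.75 = 45.3, rounded up to 46. The totals are 176 and 184, against the stated 180.
- Energy intake (120 kcal, SD 143 × 1.1 = 157.3) needs only 27 or 28 per group before dropout, so VAS drives the size.

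The stated 45 per group is thus reproduced with all participants independent.

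**2. Design effect.** Take a group of n participants, a share p of them in two-person households, change variance σ² and within-household correlation of change ICC. There are np/2 pairs, so

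Var(sum) = nσ² + 2 × (np/2) × ICC × σ² = nσ²(1 + p × ICC).

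Hence DEFF = 1 + p × ICC. If p is similar in the four groups, the same factor applies to every contrast of group means, including the factorial main effects and interaction.

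- Understatement of the SE = 1 − 1/√DEFF
- Actual two-sided type I error = 2 × [1 − Φ(1.96/√DEFF)]

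**3. Results.** The article gives neither p nor ICC, so both are assumed. Of 180 participants, p = 5% is 9 people, 20% is 36 (18 pairs) and 40% is 72 (36 pairs).

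| p | ICC | DEFF | SE understated | Type I error | N matching 180 independent | VAS power, 34 completers per group |
|---|---|---|---|---|---|---|
| 5% | 0.1 | 1.005 | 0.2% | 5.1% | 181 | 0.809 |
| 10% | 0.3 | 1.03 | 1.5% | 5.35% | 186 | 0.799 |
| 20% | 0.3 | 1.06 | 2.9% | 5.7% | 191 | 0.787 |
| 40% | 0.5 | 1.20 | 8.7% | 7.4% | 216 | 0.734 |

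Without clustering, VAS power at 34 per group is 0.811. Simulated t-tests that ignore the pairs, at 34 and 68 per arm and p of 10–40%, rejected in about 5.1–7.8% of runs, within about 0.5 percentage point of the formula.

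**4. Which model term corrects it.** Take 68 per arm with 14 pairs (28 people) and 40 singles, and a change variance of 2 per person.

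- No household term: SE = √(2 × 2/68) = 0.2425.
- Household random intercept, variance 0.5: it is the same before and after, so it drops out of each person's change. The SE stays at 0.2425.
- Household-by-time component, variance 0.5 at each time: the covariance of change within a pair is 2 × 0.5 = 1, so ICC = 1/2 = 0.5. Information per arm is 40/2 + 14 × 2/(2 × 1.5) = 29.33, and SE = √(2/29.33) = 0.2611.

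With complete data, only the last of these moves the time-by-treatment contrast.

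**The case against.** The strongest case on the other side has four parts.

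- **The rule is a contingency.** Nothing in the article says that any shared household enrolled, and both members would have to meet Table 1. This stands. A reader might infer that the standard errors are certainly too small, but the documents support only a conditional statement.
- **The correlation may be low.** The primary outcomes are VAS ratings after a fixed laboratory breakfast and intake at one weighed test meal, and stable similarity within a couple cancels from a change. Dietary counselling is described as individual, and sachets are logged per participant, so one should not infer that household members share the counselling. This also stands. An ICC of 0.5 is an upper assumption, and the correlation may be lower for the laboratory outcomes than for diet or activity.
- **The sequence is not stated.** A reader might infer that the second member simply follows the first and is not randomised. The article says only that members go to the same group. They may be allocated together, in which case neither is uniquely the randomised one.
- **This is a condensed article with an unseen analysis plan.** A count of pairs or a household sensitivity analysis could well be in that plan, and their absence here is not held against the article. That does not dispose of the point, because the article does list the model's fixed and random effects, and that list does not match its own allocation rule.

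**Conclusion.** The mismatch between allocation and model is in the text. Its effect is conditional on at least one shared household having enrolled and on positive within-household correlation of change. Under the assumed p of 5–40% and ICC of 0.1–0.5, the standard error is understated by about 0.2–8.7% and the type I error is about 5.1–7.4%; at p 20% and ICC 0.3 it is about 5.7%. At the top of the range the true standard error is 9.5% larger than the reported one (√1.20 = 1.095), which is the same thing as an 8.7% understatement.

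This is probably a minor to moderate flaw. With few pairs it is negligible, and a count of shared households would show whether it matters.

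**What to change.** Carry a household identifier in the analysis data set. In the primary and secondary models, use one of the following:

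- household-clustered standard errors with a small-sample correction;
- a household-by-time random effect in the pre/post model;
- a household random effect in a model of change or of baseline-adjusted follow-up.

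Do not rely on a household random intercept alone in the pre/post model. Report the number of shared households in each group, and add a sensitivity analysis keeping one member per household, with the rule for choosing that member fixed in advance.

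The Trial status section reports that recruitment and final visits are complete, so the allocation cannot change but the analysis can. The cost is one identifier, one change to the variance model and slightly wider confidence intervals.
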